### Consensus meeting

Professionals and health care users who have completed all three rounds of the Delphi survey and responded to at least 90% of the outcome domains in round 3 will be eligible to participate in the consensus meeting. As far as possible, allocated places will maintain the balance across stakeholder groups (e.g. 50% health care users/50% professionals) and will include non-UK, non-native, English language speakers. The purpose will be to agree a final Core Outcome Domain Set for each intervention category. Separate discussion within each meeting will include anonymised voting on each outcome as either ‘In’ or ‘Out’ (e.g. using electronic keypads which will create histograms and descriptive statistics ‘live’, to be displayed in the meeting).

### Consensus criteria

Consensus recommendations for each intervention category will be guided by the respective round-3 results. We will include domains for which 70% or more of the participants in each stakeholder groups score 7–9, and fewer than 15% score 1–3 [30]. We will exclude domains for which 70% or more of the participants in each stakeholder groups score 1–3, and fewer than 15% score 7–9 [30]. These decisions will be taken without further discussion because time at the consensus meeting will be limited. At the consensus meeting, the moderated discussion, voting and decisions will be guided as follows:For outcomes recommended to be included based on the round-3 analysis (70% scored 7–9), domains will be included if at least 70% of participants vote ‘In’For outcomes where at least 50% of more than one stakeholder group scored 7–9 on the round-3 analysis, domains will be included if at least 70% of participants vote ‘In’For outcomes where less than 50% of the participants in all stakeholder groups or at least 50% of only one stakeholder group scored 7–9 on the round-3 analysis, domains will be included only if at least 70% of participants vote ‘In’

If consensus is not reached after two rounds of voting, a ‘majority rules’ approach will be applied.

In the very final step, the Study Management Team will seek to establish a common cross-cutting Core Outcome Domain Set by identifying those outcome domains that were voted for inclusion in all three intervention-specific Core Outcome Domain Sets.

### Observational cohort study

We aspire to conduct a prospective observational cohort study to determine if participation of clinical researchers in the Delphi process increases uptake of the recommended Core Outcome Domain Sets for trials of sound-, psychology-, and pharmacology-based interventions for chronic subjective tinnitus in adults, compared with researchers who did not participate. This investigation will be conducted on the basis of the implementation of the recommendations in published reports of clinical trials in the 7 years after the Core Outcome Domain Sets are published.

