### Aims

The primary aims of the COMIT’ID study are to:Establish three Core Outcome Domain Sets, one for each of the main intervention strategies (sound-, psychology-, and pharmacology-based)Identify the key outcome domains that are common across all three Delphi processes. 

Two secondary aims are to:3.Identify the strengths and limitations of the study design with respect to methods for recruiting and for reducing attrition of health care users4.Investigate whether participation by professional experts in the Delphi process affects their subsequent use of the Core Outcome Domain Set, compared with those who do not participate.

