### Research steering group

A Research Steering Group has been appointed to oversee and manage the project. The group comprises international colleagues representing the identified intervention approaches (HFH, BM, AL), a patient and public involvement and engagement manager (AH) two health care users with lived experience of tinnitus, referred to as Public Research Partners (VC, BT), and the Study Management Team (KF, HS, DAH). The role of the Research Steering Group is to:Support the development of the study protocol, specifically commenting on the feasibility of the Delphi process, reviewing study documentation (e.g. advertisements, Information Sheets, video instructions for the survey, website content) and to participate in a pilot of round 1 of the Delphi surveyReview the list of outcome domains and associated descriptions, specifically commenting on the readability of the outcome descriptions, the appropriateness of the grouping of outcomes into categories and providing any additional outcomes that they believe should be included in the first round.

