All enrolled Delphi panellists will be eligible to register their interest in attending a 1-day consensus meeting. However, allocation of places will be limited to those respondents who complete all three rounds of the online survey. None of the Research Steering Group members will be allowed to vote on domains in the consensus meetings because this risks inadvertently introducing a power differential across participants, but they can enrol in the online Delphi surveys (with the exception of KF and HS who will have access to the dataset for all analyses). Each expert panellist is permitted to enrol for more than one Delphi process if they meet the eligibility criteria, but would be invited to attend only one consensus meeting.

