### Analyses

The data from each Delphi round will be subjected to descriptive statistics, such as number completing each round, gender, country, region, native English language speaker (or not), and retention rate at rounds 2 and 3. We will plot the distribution of rating scores within each stakeholder group (including the ‘unable to score’ option and any missing data), and we will investigate attrition bias by comparing these plots across participants who complete successive rounds versus those who withdraw at rounds 2 or 3 [31]. We will also compare the distribution of rating scores for native and non-native English language speakers. Withdrawal and language are both factors that may affect how representative the final consensus might be of the target population. A separate analysis will assess the shifts in scores across rounds as a consequence of considering the anonymised feedback from other participants. The distribution of the scores for each outcome domain will be calculated for each stakeholder group within each intervention-specific Delphi survey.

The data from the feedback questionnaire will comprise open-text responses and these will be analysed using a thematic analysis approach to address one of the secondary objectives. Uptake of the recommendations will be analysed by calculating the number and proportion of authors who have implemented and referenced the COMIT’ID study recommendations in trials reported up to 7 years after their publication, comparing data between groups using non-parametric statistics (*p* < 0.05).

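### Steering Group members who enrol as clinical researchers would count as participants in the uptake comparison, which can bias it towards a participation effect

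*Protocol article*

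**What the plan says.** The fourth aim (Aims) is to "Investigate whether participation by professional experts in the Delphi process affects their subsequent use of the Core Outcome Domain Set", set against those who do not take part. The section Observational cohort study gives its purpose as "to determine if participation of clinical researchers in the Delphi process increases uptake of the recommended Core Outcome Domain Sets". It thus narrows the exposed group to clinical researchers, and it describes the comparator only as "compared with researchers who did not participate". The Analyses section fixes the measure as "calculating the number and proportion of authors who have implemented and referenced the COMIT’ID study recommendations", over a window of 7 years after publication, with a non-parametric comparison at p < 0.05.

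Under Eligibility criteria for the Delphi panels, Research Steering Group members may not vote in the consensus meetings, "but they can enrol in the online Delphi surveys". Two Study Management Team members are excepted, being the ones "who will have access to the dataset for all analyses".

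On membership, the section Research steering group says: "The group comprises international colleagues representing the identified intervention approaches". It also lists an involvement manager, two public partners and the three-person Study Management Team. The group's role includes reviewing the domain list and "providing any additional outcomes that they believe should be included in the first round". None of these sections sets developers aside in the uptake comparison.

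**The concern.** Two statements in the article combine badly. One lets most of the Steering Group enrol in the surveys. The other assigns people to the uptake groups by participation and nothing else. Applied as written, a Steering Group member who enrols as a clinical researcher belongs to the participant group.

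These people oversaw the study, took part in reducing and wording the domain list, and could add to it. They have a reason to adopt the result whether or not they scored it in a survey. Because the measure counts referencing as well as implementation, citation of their own work enters the endpoint directly. Part of any observed difference could then be developers using their own set, reported as an effect of taking part in a Delphi process. That conclusion would be used to argue that inviting researchers into such studies improves uptake.

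**Working it through.** **Panel figures.** The section Panel size and justification gives ranges by stakeholder group. The minimum targets are 120 (sound) + 80 (psychology) + 60 (pharmacology) = 260. The upper targets are 180 + 120 + 120 = 420. Both stated totals are reproduced. The uptake comparison has no sample size of its own.

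**Clinical-researcher places.** Minimum 20 + 20 + 10 = 50; upper 30 + 30 + 20 = 80. One person may enrol in more than one survey, so the number of distinct people may be lower.

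**Members who could be affected.** The Steering Group has nine members: three international colleagues, one involvement manager, two public partners and three Study Management Team members, two of whom are barred from enrolling. The three international colleagues and the remaining team member make at most about four who might enrol as clinical researchers. This is an assumption; the article does not state their stakeholder group.

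**Formula.** Let N be the participants counted, k the developers among them, and p the uptake in everyone else, with no true participation effect. Assume that every developer uses the set. Expected participant uptake is [(N − k)p + k]/N, so the excess over p is k(1 − p)/N.

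With k = 4:

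| N | p = 10% | p = 30% |
|---|---|---|
| 50 | 4 × 0.9/50 = 7.2 points | 4 × 0.7/50 = 5.6 points |
| 80 | 4 × 0.9/80 = 4.5 points | 4 × 0.7/80 = 3.5 points |
| 20 (assumed number who author a trial) | 4 × 0.9/20 = 18 points | 4 × 0.7/20 = 14 points |

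The excess is proportional to k: with two developers, N = 50 and p = 10%, it is 3.6 points.

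**If the two barred members were in the comparator.** With an assumed 100 comparators, m = 2 developers there would raise comparator uptake by m(1 − p)/100. That is 1.8 points at p = 10% and 1.4 points at p = 30%. At p = 10% and k = 4 the net differences become:

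- N = 50: 7.2 − 1.8 = 5.4 points
- N = 80: 4.5 − 1.8 = 2.7 points
- N = 20: 18 − 1.8 = 16.2 points

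**Effect on the test.** The table gives the rejection probability of a two-sided Fisher exact test at 0.05 with 100 comparators, p = 10% and no true effect. The article names no specific test, so the choice of Fisher and of two sides is an assumption.

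| N | No developers | 4 among participants | 4 among participants, 2 among comparators |
|---|---|---|---|
| 50 | 0.033 | 0.164 | 0.078 |
| 80 | 0.039 | 0.108 | 0.043 |
| 20 | 0.025 | 0.51 | 0.36 |

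Removing developers from both groups returns the expected difference to zero and the rejection probability to the first column.

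**The case against.** The strongest reply is that this is an omission in a condensed article. The cohort study is only an aspiration, the full protocol and analysis plan are not shown, and exclusions from a 7-year secondary analysis are ordinary analysis-plan content. That carries weight for how firmly the point is put. It does not remove the point, because the permission to enrol and the participation-only grouping are both stated here, and together they produce the problem.

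The reply is also right that members may enrol rather than will, and that some might do so as practitioners and so fall outside the exposed group. The figures stack favourable assumptions: four enrolments, four publishing authors and certain adoption. They are an upper illustration.

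Three stronger readings are tempting and should not be drawn:

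- A reader might infer that the two barred team members count as non-participants and dilute the comparator. No section says how they are classified, whether they meet the clinical-researcher definition, or whether they would author eligible trials. If they did enter the comparator, the effect would be small and partly offsetting.
- A reader might infer that the aim concerns experts from outside the study team. It says professional experts, and an enrolled member is one. Excluding developers sharpens the question; the stated aim does not by itself require it.
- A reader might infer that the comparison is already distorted. It has not begun, and the article supports only that it can be.

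**Conclusion.** The point holds as a risk of bias towards a participation effect. As written, any Steering Group member who enrols as a clinical researcher is counted as a participant, although that person has reasons for using and citing the set that are independent of the survey.

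In the upper illustration (four such members, all publishing and all adopting, 10% uptake in everyone else) the inflation is 7.2 points at 50 clinical researchers and 4.5 points at 80. It is larger when few participants author trials, and it shrinks in proportion if fewer members enrol. Background uptake, the number of trial authors and the number of comparators are assumptions; the article gives none of them. The primary aims and the content of the Core Outcome Domain Sets are not affected.

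**What to change.** In the sections Observational cohort study and Analyses, state that Research Steering Group members, including the Study Management Team, are excluded as authors from both groups in the main uptake comparison. Report their uptake separately and descriptively, and add a sensitivity analysis that includes them.

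A further sensitivity analysis could drop trials that they co-author. This should stay optional: the measure counts authors, and dropping whole trials could also remove other participants and comparators, in numbers the article gives no means of judging.

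The change is a sentence or two. It needs no new data, since the members are known, and it can be settled before any uptake is observed. The cost is a few authors lost from a secondary, aspirational comparison. It does not deal with self-selection of those who choose to take part, which remains a separate limit of the design.

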### Analyses

The data from each Delphi round will be subjected to descriptive statistics, such as number completing each round, gender, country, region, native English language speaker (or not), and retention rate at rounds 2 and 3. We will plot the distribution of rating scores within each stakeholder group (including the ‘unable to score’ option and any missing data), and we will investigate attrition bias by comparing these plots across participants who complete successive rounds versus those who withdraw at rounds 2 or 3 [31]. We will also compare the distribution of rating scores for native and non-native English language speakers. Withdrawal and language are both factors that may affect how representative the final consensus might be of the target population. A separate analysis will assess the shifts in scores across rounds as a consequence of considering the anonymised feedback from other participants. The distribution of the scores for each outcome domain will be calculated for each stakeholder group within each intervention-specific Delphi survey.

The data from the feedback questionnaire will comprise open-text responses and these will be analysed using a thematic analysis approach to address one of the secondary objectives. Uptake of the recommendations will be analysed by calculating the number and proportion of authors who have implemented and referenced the COMIT’ID study recommendations in trials reported up to 7 years after their publication, comparing data between groups using non-parametric statistics (*p* < 0.05).

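### The uptake endpoint in the analysis section requires citation as well as use, counts authors rather than trials, and supports an association only

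*Protocol article*

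**What the plan says.** Three sections of the protocol article describe the same comparison in different terms.

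- **Aims** (fourth aim, secondary): "Investigate whether participation by professional experts in the Delphi process affects their subsequent use of the Core Outcome Domain Set", compared with those who do not take part. The exposed group is professional experts and the outcome is use.
- **Observational cohort study:** the purpose is "to determine if participation of clinical researchers in the Delphi process increases uptake of the recommended Core Outcome Domain Sets". The exposed group is clinical researchers. Uptake is judged on whether published trial reports implement the recommendations; citation is not mentioned. The study is introduced with "We aspire to conduct a prospective observational cohort study".
- **Analyses:** uptake is "the number and proportion of authors who have implemented and referenced" the recommendations, "in trials reported up to 7 years after their publication", "comparing data between groups using non-parametric statistics" with a 0.05 threshold. The unit is the author, and the outcome is use and citation together.

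The Abstract and the Discussion also say that the study will determine whether participation increases use or adoption. The article gives no number of trials, number of authors per trial, uptake rate or target difference for this comparison.

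**The concern.** Three features of the printed definition matter.

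1. **Endpoint.** Adding citation changes what is measured. Full use without citation scores as non-uptake, although a core outcome set exists to get domains measured and reported.
2. **Unit.** Which outcomes a trial measures is a property of the trial, shared by everyone on its author list. Counting authors can repeat one observation several times, and a simple two-group test would treat the copies as independent. A trial with both participant and non-participant authors puts the same outcome into both groups.
3. **Inference.** Participants volunteer on self-declared expertise, corresponding authors of earlier tinnitus trials are personally invited, and most steering group members may enrol in the surveys. People already favourable to core outcome sets may well be over-represented among participants.

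At stake is whether this secondary aim is answered on one definition of uptake, with a valid error rate, and with a conclusion that the design can carry.

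**Working it through.** The plan states no figure for this comparison, so there is none to reproduce. Apart from the recruitment targets cited under the objection, every number below is an assumption chosen to show size.

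**Step 1: endpoint definitions side by side.** Take a trial that measures all core domains and does not cite the paper. Aims: used. Observational cohort study: implemented. Analyses: not counted. The three sections do not agree on this case.

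**Step 2: effect of requiring citation.** Measured uptake = P(implement) × P(cite given implement). True implementation is set at 50% in both groups, with 90% citation among participants.

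| Citation among non-participants | Participants | Non-participants | Ratio |
|---|---|---|---|
| 90% | 0.50 × 0.90 = 45% | 0.50 × 0.90 = 45% | 1.00 |
| 70% | 45% | 0.50 × 0.70 = 35% | 1.29 |
| 50% | 45% | 0.50 × 0.50 = 25% | 1.80 |

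With equal citation there is no false contrast, although true use of 50% is understated. With unequal citation, a difference appears where use is identical.

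**Step 3: effect of counting co-authors.** With m authors per trial, an outcome fully shared within the trial, and within-trial correlation ρ of participation status, the variance of the author-level contrast is inflated by DE = 1 + (m − 1)ρ. A nominal two-sided 5% test then has actual level 2 × [1 − Φ(1.96/√DE)].

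| m | ρ | DE | Level by formula | Level by simulation |
|---|---|---|---|---|
| 3 | 0.1 | 1.2 | 7% | 7.7% |
| 3 | 0.3 | 1.6 | 12% | 11.9% |
| 3 | 0.5 | 2.0 | 17% | 16.9% |
| 5 | 0.1 | 1.4 | 10% | 10.5% |
| 5 | 0.3 | 2.2 | 19% | 18.9% |
| 5 | 0.5 | 3.0 | 26% | 26.7% |

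The simulation used 80 trials, 20% uptake, 30% of authors as participants, 4,000 runs and a chi-square test. A second simulation (60 trials, 30% uptake, 30% participants, 4,000 runs) covered the case with no clustering, ρ = 0. The level was then 4.9%, 4.7% and 5.1% for 2, 4 and 6 authors per trial. The inflation thus comes from clustering of participation; sharing the outcome is not enough by itself. Where status is mixed within a trial, the level is less affected, but that trial gives the same result to both groups and pulls any true difference towards zero.

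**Step 4: effect of self-selection.** Suppose participation does nothing, 60% of participants and 30% of non-participants already favour core outcome sets, and uptake is 50% among those in favour and 20% among the rest.

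- Participants: 0.60 × 0.50 + 0.40 × 0.20 = 38%
- Non-participants: 0.30 × 0.50 + 0.70 × 0.20 = 29%
- Ratio: 38/29 = 1.31, with no effect of participation.

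**The case against.** **Low stakes.** The cohort study is aspirational, serves a secondary aim, lies up to seven years ahead and gets one sentence of analysis in a condensed article. The choice of test, clustering and covariates could sit in a fuller plan. That stands, and their absence is not the criticism. The article does, however, print a unit, an endpoint and a causal question, and a fuller plan would have to reverse the first two.

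**Co-authors.** The text does not say that every co-author is counted. It could mean individual researchers or corresponding authors. That stands too, so the inflation is conditional. The five-author scenario is also generous: 80 × 5 × 0.30 = 120 participant entries, while Panel size and justification targets 20 + 20 + 10 = 50 to 30 + 30 + 20 = 80 clinical researchers if nobody enrols twice. It fits only if researchers recur across trials. The three-author scenario gives 80 × 3 × 0.30 = 72, within that range.

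**Citation has a purpose.** Some core domains may be measured for unrelated reasons, and citation helps to attribute use to the recommendations. This is a fair reason to record citation. It does not reconcile the three definitions, and separate reporting keeps the information.

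**Observational label.** The study is called observational and its aim is posed as a question. This softens the wording point without removing it, since the question posed is still whether participation increases uptake.

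A reader might infer that the standard errors will certainly be too small and that the endpoint is certainly biased towards participants. The documents support neither: they do not show how far participation clusters within trials, or who cites more often. Trials designed before the sets were published but reported within the window would, if equally common in both groups, dilute the contrast without favouring either group.

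**Conclusion.** The point holds in conditional form.

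- **Certain from the text:** the Analyses section requires citation where the Observational cohort study section and the Aims do not, and the exposed group changes from professional experts to clinical researchers to authors.
- **Conditional on citation habits:** the endpoint favours participants if they cite more often. At 50% true use and 90% against 70% citation, the spurious ratio is 1.29.
- **Conditional on counting co-authors and on clustering:** the type I error is roughly 8% to 27% for three to five authors and ρ of 0.1 to 0.5, and about 5% with ρ = 0. Mixed-status trials blur the contrast.
- **Inference:** an unadjusted comparison of self-selected participants with non-participants supports an association only.

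Because the aim is secondary and the cohort is only aspired to, this is worth correcting before outcome data exist, but it does not touch the primary aims.

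**What to change.** 1. Make implementation of the core domains in the trial report the main uptake endpoint, and report citation separately.
2. Use the trial report as the unit, with exposure defined in advance: for example, whether the corresponding author took part, or whether any author did. The any-author rule makes long author lists more likely to count as exposed, so it needs author count taken into account. Alternatively, keep authors as the unit and cluster the inference by trial or research team. With trials as units, repeated trials by one team still need handling.
3. Name one exposed group, clinical-researcher participants, in the Aims, Observational cohort study and Analyses sections.
4. Replace *increases* and *affects* by *is associated with* in those sections, and align the Abstract and Discussion.

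Restricting to trials started after the sets were published can be a sensitivity analysis; it needs a start or registration date per trial. Adjustment for earlier use of the domains, drawing on the review of 228 trials, is optional: the documents do not show that it holds data by research group.

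**Cost:** the same papers are read, with each report scored for the core domains. There are fewer effective units than authors, so intervals will be wider.
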